### Ethics approval and dissemination

All participants will be informed about the study procedures and will give their approval through informed consent before inclusion. All data collected during the study will be confidential. All participants receive a final report with their results to know their values at baseline and the end of the study. The trial will be conducted following the Declaration of Helsinki, and the study has been approved by the institutional ethics committee of the Catholic University of Murcia (CE111908).

Based on previous studies, groups larger than 30 were required for the result to reliably characterise precision error or change during clinical monitoring.^9^ A dropout rate of 16% will be assumed based on previous studies,^10^ so a minimum of 35 participants will be included per group. The RStudio V.3.15.0 software will be used to calculate the sample size. The sample size and statistical power were established considering the SD (4.2) in the maximum voluntary isometric contraction (MVIC).^11^ A significance power of 95% (1-β=0.95) and a significance level of 0.05 will be considered. Ultimately, the sample consisted of a minimum of 60 participants per group. This resulted in an assumed error of 1.06.

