### Inclusion and exclusion procedures

To be included in the study, participants will have to meet the following criteria: will be male or female, aged 50 years or older, being physically independent, not having any pathology incompatible with the study, not having participated in a structured exercise programme for at least 1 year and signing the informed consent form. The exclusion criteria will be self-reported substance abuse or dependence disorder (alcohol, non-prescribed medications, etc), being under medical prescription for taking medications that could influence physical performance, suffering from any pathology contraindicated for the exercise programme or requiring specialised medical attention (infectious, renal, pulmonary, coronary diseases, etc), having low adherence during the programme or performing physical exercise outside the study. During the pre-test phase, health personnel will perform an ECG on each participant to corroborate their cardiac health just after signing the informed consent and before the assessment tests.

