## Statistical analysis

The qualitative variables will be summarised in frequency. In contrast, the quantitative variables will be summarised using mean and SD for the TG and CG across the assessment time points. To ensure rigorous statistical evaluation, special attention has been given to controlling the type I (alpha) error and Bonferroni’s correction will be used to achieve p=0.005 for statistical significance. To compare characteristics between and within groups, the principle of intention to treat will be applied, with adjustments made to adhere to the exercise programme. The following tests will be employed to assess baseline characteristic differences between the two groups: Student’s t-test for parametric numerical variables, Mann-Whitney test for non-parametric variables and χ^2^ test for categorical binary variables.

To compare changes within and between the TG and CG across baseline and follow-up assessments, the subsequent tests will be used: for variables exhibiting normal distribution, repeated measures analyses of variance. Given the multiple comparisons involved, post hoc analyses will be conducted using t-tests with Sidak corrections to control the type I error rate; for non-parametric variables, the Friedman test will be followed by the Wilcoxon test, and, to address the multiple comparisons, the Bonferroni correction will be applied.

SPSS V.25.0 statistical software will be used in all the analyses. A p value<0.05 will be used to determine significant differences; however, this will be adjusted appropriately in the presence of multiple comparisons, as detailed above.

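### Each outcome's test is chosen by its observed distribution, and the non-normal branch, as written, does not compare the training group with the control group

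*Protocol article*

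**What the plan says.** The Statistical analysis section of the protocol article introduces its main tests with the aim "To compare changes within and between the TG and CG across baseline and follow-up assessments". It then splits by distribution: "for variables exhibiting normal distribution, repeated measures analyses of variance", with Sidak-corrected post hoc t-tests, and "for non-parametric variables, the Friedman test will be followed by the Wilcoxon test", with a Bonferroni correction. No outcome is placed in either branch beforehand. The article does not say how normality is judged, or whether on raw values, changes or residuals. A Mann-Whitney test is named only for baseline differences between the groups.

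Table 2 schedules one baseline and one post-programme assessment per arm. Under Inclusion and exclusion procedures, participants "will be male or female, aged 50 years or older"; the described analysis has no term for sex. Maximum isometric strength is listed among the primary outcomes, and an MVIC SD of 4.2 enters the sample-size text (under Ethics approval and dissemination), which ends: "Ultimately, the sample consisted of a minimum of 60 participants per group" and "This resulted in an assumed error of 1.06".

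**The concern.** Two features combine. First, the test for a primary outcome is not fixed: it depends on how the trial's own data happen to look. The criterion also concerns the variable, whereas a two-visit repeated measures ANOVA relies on the within-arm distribution of change. A mixed-sex raw variable can look non-normal while the changes are perfectly normal.

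Second, the two branches do not answer the same question. The ANOVA has a group-by-time term that compares the arms. Friedman and Wilcoxon signed-rank tests on two visits ask whether values moved over time. An outcome sent there loses its randomised comparison, and the reader is left to contrast a p value in one arm with a p value in the other.

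**Working it through.** 1. **The plan's own figure.** The sample-size text gives SD 4.2, 60 per group and an error of 1.06. The 95% half-width of a single mean is 1.96 × 4.2/√60 = 1.063; inverted, n = (1.96 × 4.2/1.06)² = 60.3. So 60 reproduces as the precision of one group's mean. Detecting a between-group difference of 1.06 at 95% power and two-sided 0.05 would need 2 × (1.96 + 1.645)² × 4.2²/1.06², or 409 per arm. Neither branch of the analysis was sized.

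2. **What the ANOVA needs.** With two arms and two visits, the group-by-time test is equivalent to a t-test on change (post minus baseline). A constant difference between the sexes cancels in the change but stays in the raw value.

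3. **How often a normal outcome is diverted.** Assumptions, none of them in the article: 60 per arm, values normal within sex, within-sex pre-post correlation 0.8, 70% women, Shapiro-Wilk at 0.05 in each of the four arm-by-visit cells, and one failure diverts. For four independent cells, chance alone gives 1 − 0.95⁴ = 18.5%. Ranges below span separate simulation runs (Monte Carlo error about 1-3 percentage points).

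| Sex gap (within-sex SDs) | Diverted, raw values checked |
|---|---|
| 0 | 17-19% |
| 1.5 | 21-24% |
| 2 | 36-40% |
| 2.5 | 72-73% |
| 3 | 94-95% |

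The same check on the changes, one test per arm, fails about 10% of the time, which is nominal (1 − 0.95² = 9.75%).

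Under a milder rule, one test on all 120 raw values with 20-50% of one sex, rejection is about 5% with no gap, 5-6% at 1 SD, 5-12% at 1.5 SD, 13-33% at 2 SD, 45-73% at 2.5 SD and 84-96% at 3 SD. Under either rule the sex mix matters only from about 2 SDs.

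4. **Whether the check protects anything.** With 60 per arm and lognormal (sigma 0.5), exponential or t(3) changes, the t-test on change had type I error 4.6-4.9% at 0.05 and 0.3-0.5% at 0.005 (20,000 runs each).

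5. **What the second branch tests.** Suppose there is no treatment effect and both arms gain equally by 0.2, 0.3 or 0.4 SD of change (assumed; 60 per arm, tests at 0.05).
   - Friedman on all 120 people at two visits is (2k − 120)²/120, with k the number who increased. It rejects in 43%, 75% and 94% of trials: it detects the shared gain.
   - Wilcoxon within each arm gives a significant training group and a non-significant control group in 22%, 24% and 13% of trials.
   - A Mann-Whitney test comparing the arms' changes rejects in about 5%.

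6. **Switch and second branch together.** Using the four-cell rule of step 3 and an equal gain of 0.2 baseline SD in both arms, the simulated null error of the whole procedure is about 7-22% over the range of sex gaps. A rough check agrees. With correlation 0.8 the SD of change is √(2 × 0.2) = 0.632 within-sex SDs, so the gain is 0.2/0.632 = 0.32 SD of change, where step 5 gives about 24%. Mixing gives 0.17 × 24% + 0.83 × 5% = 8% with no sex gap, and 0.95 × 24% + 0.05 × 5% = 23% at 3 SDs.

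7. **The same switch with a between-arm rank test.** Replacing the second branch by Mann-Whitney on changes, null rejection was 4.3-6.0% against 4.4-6.2% for always using the t-test. Power at an effect of 0.6 SD of change was 89-91% for both. The two verdicts differed in about 2-4% of trials.

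**The case against.** The strongest reply is step 7: with normal changes and a sound second branch, choosing by distribution costs almost nothing. That stands. The harm comes from the switch leading to a branch that does not compare the arms, not from the switch alone.

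The article also does not say that raw values are checked. Its introductory phrase refers to comparing changes, so a check on changes or residuals is a compatible reading; the sex mix would then drop out and only chance diversion would remain. Details of such a check may properly sit in an analysis plan that is not shown, so their absence is not the point. The rule is written in advance and turns on shape rather than on the treatment effect, and variables could be classified on baseline data alone. These replies limit the size of the problem. They do not assign any outcome to a branch or supply a between-arm test.

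Wilcoxon could also be taken to mean the rank-sum test. As a follow-up to Friedman, in a section that uses the name Mann-Whitney for its between-group rank test, signed-rank is the natural reading.

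Two stronger inferences are tempting and fail. A reader might infer that the switch can displace the analysis on which the trial was sized; step 1 shows that the stated 60 is the precision of one mean, so no comparative analysis was sized. A reader might also infer that outcomes would be reported on different scales; the same section summarises every quantitative variable by mean and SD whichever branch applies, so only the test would differ.

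**Conclusion.** The point holds in this form: the plan lets each outcome's observed distribution choose its test, and the branch for non-normal outcomes, as written, gives no comparison of training with control. That the test depends on the data, and that the second branch works within an arm, follows from the text and the two-visit schedule.

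The sizes are conditional. Chance diversion of a truly normal outcome is about 5% for a single pooled check and 17-19% for the four-cell rule. A material contribution from the sex mix needs raw values to be checked and a gap of about 2 within-sex SDs or more; the article gives neither. The 7-22% null error further assumes an equal gain in both arms and that a significant training group beside a non-significant control group is read as an effect. The within-arm rates in step 5 use 0.05; they were not worked out for the 0.005 threshold that the plan also states. It should be corrected before analysis, since the correction is cheap and a primary comparison can otherwise be lost.

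**What to change.** Delete the choice by normality. Name in advance one between-group model for every continuous outcome, used whatever the raw distribution: for example, an ANCOVA of the post-programme value on group, adjusted for baseline and with sex as a covariate. Check the model on its residuals. Keep a bootstrap, log-scale or between-arm rank analysis of change as a sensitivity analysis only. Reserve a between-arm rank or ordinal method for outcomes that are ordinal by construction, such as the 0-12 SPPB score, and remove Friedman and within-arm Wilcoxon as the route to any between-group conclusion.

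The cost is analysis-plan wording; no data collection changes. The downside is small: a rank test would have somewhat more power for an outcome whose changes are truly heavy-tailed, and the sensitivity analysis would show that.

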## Abstract

This project will investigate the effectiveness of an 8-week outdoor fitness equipment (OFE) programme on health parameters in healthy community-dwelling middle and older adults, corresponding to the present paper to the study protocol, which follows a single-blind randomised controlled trial design. The training intervention will involve participation in an OFE programme implemented over 8 weeks, two sessions/week. Rating of perceived exertion, heart rate, training volume and adherence to the exercise programme will be registered each session. The control group will not receive any structured exercise programme. Blinded examiners will evaluate before and after the training programme muscle strength with both maximum knee extension and elbow flexion isometric tests, handgrip strength test and five time sit-to-stand test; cardiovascular fitness with 400-metre walking test; postural stability with the balance tests of the short physical performance battery (SPPB) battery; dynamic balance with Timed Up and Go (TUG) test; body composition with dual-energy X-ray absorptiometry; functional performance by gait speed, TUG and SPPB battery; blood pressure; and sagittal spine disposition and pelvic tilt. Information will also be collected about demographic characteristics, health-related quality of life, satisfaction with life and adherence to the Mediterranean diet questionnaires. After that, sarcopenia, osteoporosis and fracture risk will be calculated. The results derived from this research will increase the knowledge of the effectiveness of OFE training for improving the health of healthy community-dwelling middle and older adults.

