The hypothesis is that the OFE training for 8 weeks, twice per week, improves physical fitness, body composition, psychological state and prevention of the effects of ageing after the intervention period compared with the daily activities control group (CG).

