#### Sarcopenia

The HG and chair stand tests will assess muscle strength (muscle quality). Muscle quantity will be measured through appendicular skeletal muscle mass with DEXA values, and functional performance will be measured by 4 m gait speed, TUG and the SPPB battery. The risk associated with each variable will be defined in connection with the EWGSOP2 (European Working Group on Sarcopenia in Older People) sarcopenia cut-off point.^18 19^

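### The tests named for non-normal outcomes (Friedman, then Wilcoxon) are within-subject tests and cannot make the between-group comparison that the plan says they will make

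*Protocol article*

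**What the plan says.** Three statements in the Statistical analysis section of the protocol article bear on this point.

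- Purpose of the outcome tests: "To compare changes within and between the TG and CG across baseline and follow-up assessments, the subsequent tests will be used".
- Tests then named: "for variables exhibiting normal distribution, repeated measures analyses of variance", with Sidak-corrected t-tests afterwards, and "for non-parametric variables, the Friedman test will be followed by the Wilcoxon test", with a Bonferroni correction.
- Independent-samples tests: these sit in the preceding paragraph, under the statement "The following tests will be employed to assess baseline characteristic differences between the two groups". That list contains the "Mann-Whitney test for non-parametric variables", alongside Student's t-test and the chi-square test.

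Two facts from elsewhere in the article matter. The hypothesis at the end of the Introduction is comparative: training is expected to do better than the control condition. There are two assessments per outcome, baseline and post (Table 2). The Abstract says the same: "Blinded examiners will evaluate before and after the training programme muscle strength".

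**The concern.** A parallel-group trial answers its question by comparing the arms. Repeated measures ANOVA can do that through a group-by-time term, so the normal-data branch has a route to the hypothesis. The non-parametric branch has no counterpart. Its tests ask whether people changed between two visits, not whether one arm changed more than the other.

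Anything that moves both arms alike, such as familiarity with a test, season or regression to the mean, registers as change in such a test. If significance in TG, or significance in TG and not in CG, is then taken as evidence for the programme, the error rate is no longer the nominal one. The outcomes that might enter this branch include some listed as primary. The SPPB is a bounded 0 to 12 score, and centre-of-pressure measures may be skewed. The article gives no distributions, so which outcomes are affected is unknown.

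**Working it through.** **1. What the named tests compare.** The plan gives no figure on this point, so the core is a matter of test definitions.

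- Friedman ranks the repeated measurements within each person. It has no term for an independent group. With two assessments, n people and k of them improving (no ties), the statistic is (2k − n)²/n on 1 degree of freedom, which is the sign test.
- Wilcoxon as the follow-up to Friedman is the signed-rank test on paired differences. The same section calls its independent-samples rank test Mann-Whitney and lists it for baseline only, which supports this reading.
- Run in each arm, these tests give two separate answers. Run on both arms pooled, they give one answer about everybody. Neither is TG against CG.

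**2. Inputs for an illustration.**

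- 60 per group: from the sample-size text, which stands under Ethics approval and dissemination.
- Thresholds 0.05 and 0.005: both are stated in Statistical analysis, so both are shown.
- Assumed, because the documents give no value: zero training effect, normal change scores with SD 1, and the same shift of 0.3 SD in both arms.
- TG counts as significant only if Friedman and Wilcoxon both pass, as the plan's sequence implies.

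**3. Check by hand on the Friedman step.** The probability that a person improves is Φ(0.3) = 0.618. The number improving out of 60 then has mean 37.07 and SD √(60 × 0.618 × 0.382) = 3.76.

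- At 0.05 the test needs (2k − 60)²/60 > 3.84, so k ≥ 38. The normal approximation gives z = (37.5 − 37.07)/3.76 = 0.11, a probability of about 45%.
- At 0.005 it needs (2k − 60)²/60 > 7.88, so k ≥ 41. Here z = (40.5 − 37.07)/3.76 = 0.91, about 18%.

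The two-step rate must lie a little below these values, and it does.

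**4. Simulation results, shared shift 0.3 SD, no training effect.**

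| Result | at 0.05 | at 0.005 |
|---|---|---|
| TG significant on Friedman and Wilcoxon | about 44% | about 16% |
| TG significant, CG not | about 25% | about 14% |
| Mann-Whitney on change, TG against CG | about 5% | about 0.4% |

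The arms are independent, so the second row should equal p(1 − p): 0.44 × 0.56 = 0.25 and 0.16 × 0.84 = 0.13. This agrees within simulation error of about one percentage point.

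**5. Range.**

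- At a shared shift of 0.4 SD, the two-step rate is 68% at 0.05 and 36% at 0.005. TG significant and CG not is then 0.68 × 0.32 = 22% and 0.36 × 0.64 = 23%.
- With measurements drawn from a skewed distribution and shifts of 0.2, 0.3 and 0.5 SD, the two-step rate at 0.05 is 34%, 69% and 98%. TG significant and CG not is 0.34 × 0.66 = 22%, 0.69 × 0.31 = 21% and 0.98 × 0.02 = 2%. Mann-Whitney on change stays between 4.6% and 5.6% at 0.05, and at 0.4% to 0.5% at 0.005.

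**The case against.** Several points on the other side are fair.

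- **The comparison is intended.** The section says it will compare between groups, and Study design and setting also speaks of interpreting results within and between groups. This stands. The fault is that the tests named cannot do it, not that the authors forgot the control group.
- **Wilcoxon might mean the rank-sum test.** The article does not say signed-rank. Its place after Friedman, and the separate use of the name Mann-Whitney, make the paired reading the natural one. If rank-sum on change scores is meant, the text has to say so.
- **The control group is tested too.** This stands. A large shared shift would usually show in CG as well: at 0.4 SD both arms pass the two steps in 0.68 × 0.68 = 46% of trials at 0.05, a pattern that should warn a reader. With equal shifts, TG significant and CG not can never exceed p(1 − p) = 25%.
- **Learning is not equally plausible everywhere.** DEXA and blood pressure are not obviously learnable, handgrip has a familiarisation repetition, and several tests take the best of two or three attempts. This limits the size of any shared shift but does not exclude one.

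A reader might go further and infer that practice effects will be reported as training benefit, or that much of the outcome list has lost its randomised comparison. The documents support neither. No sentence makes a within-TG p value the criterion for efficacy, and no distributions are given. Outcomes judged normal go to repeated measures ANOVA, which can test group by time. A reader might also count the lack of a follow-up test for sarcopenia categories. That is an omission which a condensed article may leave to the full plan, and it is no part of this point.

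**Conclusion.** The non-parametric branch is wrong as written. It is offered as a comparison within and between TG and CG, but on the natural reading its two tests deliver only the within-group half. Followed literally, the hypothesis goes untested for every outcome judged non-normal. This conclusion rests on what the tests are and needs no simulation.

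The size of the practical risk does rest on assumptions: a shared shift that the documents do not give, no true training effect, and 60 per arm. The stricter 0.005 threshold lowers the false signals but does not remove them, because it corrects for the number of tests and not for the missing comparison. The 0.3 SD example lies close to the 25% ceiling for the discordant pattern at 0.05, so it should be read as an illustration and not as a forecast.

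**What to change.** In Statistical analysis, name a between-arm test for outcomes that are not normal. The minimum is a Mann-Whitney test of TG against CG on the change scores. A rank-based or robust ANCOVA of the post value, adjusted for baseline, is an alternative. State that this comparison is the basis for any conclusion about efficacy. Keep Wilcoxon signed-rank results within each arm as description, and say explicitly that the test is signed-rank. Friedman can be dropped, since with two assessments it is only a sign test.

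The cost is a sentence of analysis wording. No new data, visits or participants are needed.

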## Conclusions

This protocol presents a randomised controlled trial to evaluate the efficacy and safety of an exercise programme with OFE designed to improve physical and psychological health variables.

Exercise and strength training are essential to prevent or reverse disease, maintain or improve health and prevent loss of function in adults, middle-aged and older people. This is where free and free training with OFE in outdoor spaces can be relevant to health. However, no specific indications are available on the appropriate training programme and which machinery can be safe and effective for their physical, psychological and social health. A design study is presented in this research, the results of which are as follows, which could provide evidence to physicians, exercise trainers and policymakers on the best strategy to ensure safe and effective outdoor exercise, establishing parameters for prescribing and monitoring a training programme with OFE, while respecting individual progress.

